### Outcomes

The primary outcome measure will be the minimum threshold reduction in VTE risk in the probability trade-off exercise at which women switch from declining to accepting LMWH prophylaxis (which we will refer to as the “VTE threshold”).

Secondary outcomes will include:

(i) women’s willingness to take prophylactic LMWH according to their classification as either high or low risk for recurrence,

(ii) women’s willingness to take prophylactic LMWH for each of the three hypothetical scenarios

(iii) Utilities for each of the five health states assessed in the FT (the burden of prophylactic LMWH use during pregnancy – either the standardized experience or the patient’s prior experience-, a pregnancy with the participant’s own most recent VTE, a standardized description of pregnancy-related DVT, a standardized description of pregnancy-related PE, and a standardized description of an obstetrical bleed [Additional file 1: Appendix I]).

**Figure 4 F4:**
[figure not shown]
**Markov state transition decision model used in analysis**. This diagram depicts the model used in the analysis. In the figure on the top, the square on the left represents a “decision node” from which 2 branches, representing alternative management strategies emanate. Each strategy leads to the same Markov node, represented by a square with the “∞” symbol. The branches leading from the Markov node represent the various potential health states that patients pass through during the model simulation. Although the potential states for each strategy are the same, the initial distribution among states and probabilities associated with transitions between states will differ between strategies. The figure on the bottom is the modeled adverse events. During each time period or “cycle”, modeled patients are at risk for various adverse events. Round nodes represent the chance events. For each patient, the sequence of outcomes at these “chance” nodes will determine the state at which they begin the next cycle.

### Analysis

#### Baseline characteristics

We will describe age, educational attainment, pregnancy status, number and characteristics of previous venous thromboembolic events, presence or absence of precipitating risk factors, and prior experience with prophylactic LMWH injections using means and standard deviations or proportions, as appropriate.

#### Primary and secondary outcome(s)

We will calculate the mean threshold reduction in VTE at which women were willing to accept use of LMWH and the 95% confidence interval around the mean. We will calculate the proportion of women who are willing to take prophylactic LMWH and the associated 95% confidence intervals The mean and standard deviation of the visual analog scale ratings for each health state will also be determined.

Multiple variable linear regression will be undertaken to explore determinants of the VTE threshold, as determined in the probability trade-off exercise. In this analysis, VTE threshold will be the dependent variable and the independent variables will be the previous experience of VTE (categorized as severe, moderate, or mild), previous experience with prophylactic LMWH (yes, problematic; yes, no problems; no prior experience), level of education (some postsecondary versus no postsecondary) and study site.

We will perform a standard multiple variable logistic regression to explore the determinants on the choice for or against LMWH prophylaxis in the real life scenario. The dependent variable will be the choice for or against LMWH prophylaxis and the independent variables will be the previous experience of VTE, previous experience with LMWH prophylaxis, level of education, study site, and high or low risk for recurrence.

A hierarchical logistic regression in which the dependent variable will be the choice to receive or not receive LMWH from the results of the hypothetical scenario exercise will also be undertaken. The independent variable within the first level will be the magnitude of the absolute risk reduction (high, moderate and low). The second level, nested within the absolute risk reduction will include previous experience of VTE, previous experience with LMWH, level of education and study site. Finally, we will perform a multiple variable linear regression with the threshold as the dependent variable and with utilities as independent variables. We will evaluate the interaction term of utilities and VTE in the regression model.

Using an independent sample *t*-test, we will evaluate if the responses between women who are pregnant or planning a pregnancy are different to those who are not.

The scatter plots of each of the participants’ utilities, as determined by the FT ratings of the health states, and the VTE thresholds will be examined to evaluate the relation between participant utilities and their VTE threshold. We will calculate Pearson’s correlations between each of the utilities for the health states and the threshold.

We believe that a lack of consistency in patient responses is the best way to detect a problem with individual patient understanding, which if it occurs frequently enough (i.e. > or = 25% of participants), may represent a problem in the way in which the information is being presented. Therefore, we will review consistency data after 10, 20, 30, and 40 women have been enrolled. We will also examine consistency data prior to these pre-specified points if there is concern about the level of inconsistency in patient responses. Table 4 contains frequencies of inconsistent responses, which would favor a review of the study scripts and presentation tools. We will also compare responses between women who are consistent and those who are inconsistent in their responses, even after they are provided with the opportunity to correct discrepancies in their responses. If the results differ between these groups, our primary analysis will include only those with consistent responses.

**Table 4 T4:** Guidelines for frequencies of inconsistent responses favoring review of study scripts and presentation tools

**Frequency of inconsistent response**	**%**	**Lower bound of 95% CI**
> or = 5/10	50.0	23.7
> or = 8/20	40.0	21.9
> or = 10/30	33.3	19.2
> or = 12/40	30.0	18.1

For all key analyses above, we will compare results and the pattern of responses in women who answer the “understanding” questions correctly and those who do not. A similar comparison will also be made according to the interviewer’s impression of patient understanding. If the results differ between women categorized as understanding and not understanding, our primary analysis will focus on women with an apparent high level of understanding.

Finally, we will perform a “personalized decision analysis” for each woman in the study. We will update a prior decision analytic model examining prophylactic LMWH in pregnant women with a history of prior VTE (Figure 4) [87], using each women’s visual analog scale utility assessments for the relevant outcomes of DVT in pregnancy, PE in pregnancy, obstetrical hemorrhage and the burden of LWMH prophylaxis in pregnancy. Given that the risk of heparin-induced thrombocytopenia (<0.1%) and heparin associated osteoporosis (<1%) are either not increased or minimally increased with prophylactic LMWH [65,68], we will not consider these health states in the decision analysis. We will place the health state utilities in the decision model for each woman’s current situation and the three hypothetical scenarios. We will compare the decision model’s results with the VTE threshold selected in the probability trade-off tasks.

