**Methods:**

We will perform a multi-center cross-sectional interview study in Canada, USA, Norway and Finland. The study population will consist of 100 women with a history of lower extremity deep vein thrombosis (DVT) or pulmonary embolism (PE), and who are either pregnant, planning pregnancy, or may in the future consider pregnancy (women between 18 and 45 years). We will exclude individuals who are on full dose anticoagulation or thromboprophylaxis, who have undergone surgical sterilization, or whose partners have undergone vasectomy. We will determine each participant's willingness to receive LMWH prophylaxis during pregnancy through direct choice exercises based on real life and hypothetical scenarios, preference-elicitation using a visual analog scale (“feeling thermometer”), and a probability trade-off exercise. The primary outcome will be the minimum reduction (threshold) in VTE risk at which women change from declining to accepting LMWH prophylaxis. We will explore possible determinants of this choice, including educational attainment, the characteristics of the women’s prior VTE, and prior experience with LMWH. We will determine the utilities that women place on the burden of LMWH prophylaxis, pregnancy-related DVT, pregnancy-related PE and pregnancy-related hemorrhage. We will generate a “personalized decision analysis” using participants’ utilities and their personalized risk of recurrent VTE as inputs to a decision analytic model. We will compare the personalized decision analysis to the participant’s stated choice.

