#### The participant interview

Figure 1 presents the flow of the interview. We will determine patients' age, educational attainment, and current pregnancy status, as well as specific details about their past venous thromboembolic events (including occurrence of PE or DVT, number of events, date of the last event, presence or absence of precipitating risk factors prior to their event [Table 1]), known hypercoagulable states (Table 1), family history of VTE, type and duration of treatment for their event(s), adverse treatment effects, completeness of their recovery (for example, presence or absence of residual chest pain or shortness of breath, and/or residual leg swelling, pain or discoloration), and presence or absence of prior experience with injection of prophylactic doses of LMWH during pregnancy.

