#### Direct choice exercises

We will determine each participant’s willingness to receive LMWH prophylaxis through direct choice exercises. Women will initially complete what we refer to as the real-life scenario, followed in order by hypothetical scenarios, the visual analog scale, the probability trade-off exercise, a review of their answers, and finally questions to examine their understanding their understanding of the scenarios. Use of decision boards will facilitate patient understanding of the direct choice exercises. Descriptions of each phase of the interview follow.

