##### Real life scenario

We will initially present each woman with a decision board that will include the probabilities of developing VTE during pregnancy given the characteristics of her prior VTE (see below). This scenario will contain information similar to that received during standard clinical care but presented in a more systematic manner than that is typical in clinical practice.

For this real life exercise, we will have two potential scenarios. We will classify women as low or high risk of recurrence. We define low risk of recurrence as the absence of a known thrombophilia and prior VTE associated with a major transient risk factor within 8 weeks prior to their last event, and higher risk of recurrence as prior unprovoked VTE, VTE associated with a minor transient risk factor within 8 weeks prior to the event or any VTE in association with a known hypercoagulable state. (Table 1) We estimate that the risk of antepartum recurrence for women judged to be at lower risk lies between 0 and 5%, while that for higher risk women ranges between 5 and 10%. We will assume that prophylactic LMWH reduces the risk of antepartum recurrence by approximately 70% [71]. To ensure optimal understanding, we will present the risk of recurrence with and without LMWH prophylaxis in three different ways: table, bar chart and pictograph (Table 2 and Figures 2 and 3). 

**Table 2 T2:** Example of table presenting the risk of antepartum VTE recurrence for women considered at high risk of recurrent VTE during pregnancy

	**Without low molecular weight heparin use**	**With low molecular weight heparin use**
Probability of developing a blood clot during your pregnancy	5-10 in 100	1-3 in 100
Probability of NOT developing a blood clot during pregnancy	90-95 in 100	97-99 in 100

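### Risk class is a covariate in only one of the three determinant models, so the LMWH-experience and VTE-severity coefficients in the other two may be confounded by it

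*Protocol article*

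**What the plan says.** The subsection on primary and secondary outcomes (Analysis) gives a covariate list for each of three determinant models.

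- **Threshold, linear regression:** "the independent variables will be the previous experience of VTE (categorized as severe, moderate, or mild), previous experience with prophylactic LMWH", plus education and study site.
- **Real-life choice, logistic regression:** the same VTE and LMWH variables, plus "level of education, study site, and high or low risk for recurrence".
- **Hypothetical choices, hierarchical logistic regression:** the first level is the size of the absolute risk reduction; the second level "will include previous experience of VTE, previous experience with LMWH, level of education and study site".

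Risk class is available for everyone. Under Real life scenario the protocol says "We will classify women as low or high risk of recurrence", using provoking factors and known thrombophilia. It attaches a risk of 0 to 5% to the low class and 5 to 10% to the higher class. The class-specific board comes first: "We will initially present each woman with a decision board that will include the probabilities of developing VTE during pregnancy", and under Direct choice exercises, "Women will initially complete what we refer to as the real-life scenario, followed in order by hypothetical scenarios". The abstract lists the determinants to be explored as "including educational attainment, the characteristics of the women’s prior VTE, and prior experience with LMWH". The participant interview collects details of past events, "including occurrence of PE or DVT, number of events, date of the last event", and the precipitating factors.

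**The concern.** Class could reach the threshold and the hypothetical choices in two ways. First, each woman has already decided on a board showing either 0 to 5% or 5 to 10%, which may anchor what follows. Second, interviewers review answers across the exercises for consistency and allow changes, so a real-life choice made under one class's figures can feed back into later answers.

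Class may also be related to the listed covariates. LMWH experience means prophylactic use during pregnancy. Table 1 counts pregnancy and the postpartum period as minor transient factors, which puts VTE at those times in the higher class, together with unprovoked VTE and known thrombophilia. Such women may well have been offered prophylaxis more often.

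If both links exist, part of what is reported as an effect of LMWH experience or of severity is an effect of class. In addition, no planned analysis contrasts the primary threshold between low- and higher-risk women, although the results are meant for guideline developers and willingness by class is the first secondary outcome.

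**Working it through.** The plan states no figure on this point, so there is none to reproduce. The check compares the covariate lists, counts parameters and sizes the possible bias.

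**1. Covariate lists**

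| Model | Severity | LMWH experience | Education | Site | Risk class |
|---|---|---|---|---|---|
| Threshold (linear) | yes | yes | yes | yes | no |
| Real-life choice (logistic) | yes | yes | yes | yes | yes |
| Hypothetical choices (hierarchical) | yes | yes | yes | yes | no |

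DVT/PE type is a named term in none of the three.

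**2. Room in the threshold model**

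Inputs from the protocol: 100 women, six centers, three severity levels, three LMWH levels, two education levels. Entering site as six categories is an assumption.

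- Planned terms: 2 + 2 + 1 + 5 = 10, leaving 100 − 11 = 89 residual degrees of freedom.
- With risk class: 11 terms, 88 residual, 100/11 = 9.1 women per term.
- With risk class and DVT/PE type: 12 terms, 87 residual, 100/12 = 8.3 women per term.

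**3. Size of the bias**

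Bias in a listed coefficient = γ × δ. Here γ is the effect of class on the threshold (VTE per 100, scale 0 to 16) and δ is the difference in the share of higher-risk women between two levels of that covariate. The documents give neither, so both are assumed.

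| γ | δ = 0 | δ = 0.2 | δ = 0.3 | δ = 0.4 |
|---|---|---|---|---|
| 0 | 0 | 0 | 0 | 0 |
| 1 | 0 | 0.2 | 0.3 | 0.4 |
| 2 | 0 | 0.4 | 0.6 | 0.8 |
| 3 | 0 | 0.6 | 0.9 | 1.2 |

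One way to reach δ = 0.2: assume 75% are in the higher class, with prior LMWH use in 30% of the higher and 10% of the low class.

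- Experienced: 0.75 × 0.30 + 0.25 × 0.10 = 0.25 of all women.
- Higher class among experienced: 0.225/0.25 = 0.90.
- Higher class among the rest: 0.525/0.75 = 0.70.
- With γ = 2 the bias is 2 × (0.90 − 0.70) = 0.40.

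With an assumed SD of 4 and 25 experienced women, the SE is 4 × √(1/25 + 1/75) = 0.92, so this bias is 0.43 SE. The plan splits experience into problematic and unproblematic. With an even split the SE is 4 × √(1/12.5 + 1/75) = 1.22, and the ratio falls to 0.33.

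**4. Simulation of the threshold model**

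Assumed: n = 100, residual SD 5, LMWH levels 20/20/60%, no true LMWH effect, higher class lowers the threshold by γ; 3,000 runs per setting.

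| γ | δ | Bias, class omitted | False positives | Bias, class included | False positives |
|---|---|---|---|---|---|
| 2 | 0 | 0.04 | 4.9% | 0.03 | 4.8% |
| 2 | 0.20 | −0.41 | 5.9% | 0.00 | 4.7% |
| 3 | 0.20 | −0.63 | 7.1% | −0.02 | 5.5% |
| 3 | 0.35 | −1.08 | 11.9% | −0.04 | 5.6% |

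Across the settings with δ = 0, the false-positive rate with class omitted ran from 4.8 to 6.3%, so 5.9% cannot be told apart from no inflation. Including class raised the SE from about 1.4 to at most about 1.5.

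**5. Precision of the class contrast itself**

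Unadjusted 95% half-width, with assumed SD 4:

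- 15 low-risk women: 1.96 × 4 × √(1/15 + 1/85) = 2.2 per 100.
- 40 low-risk women: 1.96 × 4 × √(1/40 + 1/60) = 1.6 per 100.

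**The case against.** The differing lists have a plausible rationale. In the real-life exercise the displayed risk depends on class, so class belongs in that model. Elsewhere every woman sees the same figures: 4, 10 and 16 per 100 in the scenarios, and a fixed 16 per 100 without prophylaxis in the trade-off. The three common scenarios also come between the class-specific board and the trade-off, so the latest risk information is the same for all. This stands as a likely reason for the choice and weakens the anchoring argument. It does not remove it, because a common display equalises what is shown and not who answers. The protocol does not state the rationale either.

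A reader might infer that the determinants are confounded and that the reported LMWH effect is partly a class effect. The documents do not support that. It needs class to affect the threshold and also to be associated with LMWH experience or severity, and neither is shown.

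A reader might also infer that the study cannot compare thresholds by class. It can, since class is assigned to every woman; the comparison is simply not planned.

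Nor does the missing DVT/PE term contradict the abstract. Severity is itself a characteristic of the prior VTE, its grading is not given and may already reflect type, and the real-life model omits type too.

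Finally, the regressions are exploratory, and willingness by class is already a secondary outcome. Both points limit the importance of the matter.

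**Conclusion.** The concern holds as an unexplained difference in covariates that leaves a plausible source of bias in two exploratory models. The coefficients for LMWH experience and severity may be confounded by risk class. For the threshold model, an assumed class effect of 1 to 3 per 100 and a difference in class share of 0.2 to 0.4 give a bias of about 0.2 to 1.2 per 100 on the 0 to 16 scale. It is exactly zero if either link is absent. In the middle of that range the bias is under half a standard error and barely changes the false-positive rate; only the stronger combinations do so appreciably. These sizes rest on assumed SDs, class shares and covariate mixes, and none was worked out for the hypothetical-choice model. The primary mean threshold and its confidence interval are untouched.

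**What to change.** Add risk class (low or higher) to the linear regression of the threshold and to the second level of the hypothetical-choice model. Report the adjusted difference in mean threshold between classes, with its 95% CI, labelled as exploratory. If class is to stay out, state the reason.

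Say whether the severity grade already reflects DVT/PE type. Adding type is optional and makes sense only if it does not, since entering both would otherwise change what the severity coefficient means.

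No new data are needed. The cost is one parameter per model (residual degrees of freedom in the threshold model fall from 89 to 88) and a slightly larger SE for the other coefficients. If few women are low risk, the class contrast will be imprecise and should be read through its interval.

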##### Hypothetical scenarios

We will provide study participants with three standardized scenarios in which the baseline risk of recurrent VTE, with and without the use of LMWH (assuming a 70% relative risk reduction) [71], will be varied (Table 3). Interviewers will show each woman a decision board with pictograms representing a low, followed by a medium, then a high risk of recurrent VTE. Participants will express their willingness to use LMWH given the associated burden (either based on their own prior experience or the standardized description [Additional file 1: Appendix I]), and the absolute magnitude of VTE risk reduction associated with the varying VTE recurrence risks. 

**Table 3 T3:** Hypothetical scenarios with variable baseline risks of recurrent VTE and estimates of LMWH effectiveness

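### The hierarchical logistic model for the hypothetical scenarios states its nesting the wrong way round: the three choices belong within each woman

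*Protocol article*

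**What the plan says.** The model is in the Protocol article, Analysis, under Primary and secondary outcome(s), and its outcome comes from the hypothetical scenarios: "A hierarchical logistic regression in which the dependent variable will be the choice to receive or not receive LMWH from the results of the hypothetical". Its first-level predictor is the size of the absolute risk reduction, in three categories. The next sentence places the women's characteristics: "The second level, nested within the absolute risk reduction will include previous experience of VTE, previous experience with LMWH". Education and site are placed there too.

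The section on Hypothetical scenarios describes how the data arise: "Interviewers will show each woman a decision board with pictograms representing a low, followed by a medium, then a high risk of recurrent VTE". Each woman therefore gives three answers, one per risk level. The Abstract sets the size: "The study population will consist of 100 women". That makes 300 answers from 100 women.

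For the real-life scenario, where each woman makes one choice, the plan uses a different model: "We will perform a standard multiple variable logistic regression to explore the determinants on the choice for or against LMWH prophylaxis in the real life". The article does not name the woman as a unit in the three-choice model. It mentions no random intercept per woman, no GEE and no clustered standard errors.

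**The concern.** Nesting a set of units within a factor means that each unit sits in one level of that factor. Here every woman appears at all three levels, so neither she nor her characteristics can be nested within the risk reduction. What is nested is the choice, within the woman.

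The three answers of one woman will almost certainly be correlated. The study assumes that each woman has a threshold at which she moves from declining to accepting, and interviewers check that her answers agree with one another. An analyst who followed the sentence literally would group 300 answers by three risk levels and leave that correlation out. Determinants that do not vary within a woman would then look more precisely estimated than they are, and chance associations with VTE history, LMWH experience, education or site could be reported as real. The Discussion says the results are meant to inform guideline developers.

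**Working it through.** The plan gives no standard error, intraclass correlation or power for this model, so there is no stated figure to reproduce.

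**Step 1. Structure.** Inputs: 100 women (Abstract) and 3 scenarios per woman (Hypothetical scenarios), giving 100 × 3 = 300 choices. Risk level varies within a woman; prior VTE, LMWH experience, education and site do not. Risk level is crossed with women, and choices are nested within women. The written nesting contradicts this.

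**Step 2. Approximate size for woman-level determinants.** With m = 3 choices per woman and correlation r between the yes/no answers, the variance is understated by 1 + (m − 1)r = 1 + 2r and the standard error by √(1 + 2r). For r = 0.3, 0.5 and 0.7 (assumed) the factor is √1.6 = 1.26, √2.0 = 1.41 and √2.4 = 1.55. The 300 choices then carry the information of 300/1.6 ≈ 188, 300/2.0 = 150 and 300/2.4 = 125 independent ones.

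**Step 3. Simulation of a fit with no woman-level term.** 2,000 replicates per row; 100 women × 3 choices; risk level as a three-category term; one binary woman-level covariate with no true effect. The latent intraclass correlation (ICC) is assumed. Ratios come from unrounded values.

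| Latent ICC | Observed r | Empirical SD | Model SE | Ratio | √(1 + 2r) | Type I error, no woman term | Type I error, clustered on woman |
|---|---|---|---|---|---|---|---|
| 0 | 0.00 | 0.261 | 0.258 | 1.01 | 1.00 | 5.5% | 5.6% |
| 0.3 | 0.19 | 0.304 | 0.257 | 1.18 | 1.17 | 10.3% | 5.4% |
| 0.5 | 0.31 | 0.335 | 0.257 | 1.31 | 1.27 | 13.2% | 5.3% |
| 0.7 | 0.43 | 0.346 | 0.256 | 1.35 | 1.36 | 14.0% | 4.3% |
| 0.9 | 0.54 | 0.378 | 0.257 | 1.47 | 1.44 | 18.6% | 5.0% |

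The formula and the simulation agree closely.

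Two further sets of runs used a random-intercept SD on the logit scale:

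- SD 1 to 4 (latent ICC 0.23 to 0.83; 1,500 replicates): factor 1.12 to 1.32, type I error 8.5% to 13.1%; clustering on the woman gave 4.5% to 5.7%.
- SD 1 to 3: factor 1.15 to 1.43, type I error 9% to 17%; clustering gave 4% to 6%.

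**Step 4. The study's own threshold idea.** From Table 3 the absolute reductions are 4 − 1 = 3, 10 − 3 = 7 and 16 − 5 = 11 per 100. Suppose each woman accepts when the reduction reaches her personal threshold (assumed mean 6, limited to 0 to 16). With a threshold SD of 4, r is 0.35, the factor 1.29 and type I error 12.5%. With an SD of 6, r is 0.50, the factor 1.41 and type I error 16.5%. Clustering restores 4.4% and 4.8%.

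**Step 5. The risk-reduction effect.** This is a contrast within women, for which the standard-error ratio is about √(1 − r): √0.81 = 0.90 at r = 0.19 and √0.46 = 0.68 at r = 0.54. With no true scenario effect and random-intercept SD 1, 2 and 3, simulated empirical SD over model SE was 0.88, 0.77 and 0.68, with rejection in 3.8%, 1.7% and 0.8% of runs. A separate run over SD 1 to 3 gave 0.79 to 0.90. For this term the error is conservative.

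**Step 6. Readings under which the standard errors are not too small.** A random intercept per woman, with only the phrase misworded, models the correlation. So does estimating the determinants separately within a risk level, which uses one choice per woman. Simulated for the medium level, that gave type I error of 4.0% to 5.3% with correlated choices and 5.8% at ICC 0.

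**The case against.** The best defence is that the authors probably meant the right model. They use ordinary logistic regression where there is one choice per woman and switch to a hierarchical one where there are three; repeated choices are the natural reason. Risk reduction at level 1 and women's characteristics at level 2 is the assignment a choices-within-women model needs. This stands as far as it goes: a reader might infer that the planned standard errors are simply wrong, and the document does not support that. They are wrong only if the sentence is followed literally.

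It can also be said that the simulations fit a plain logistic model, not a hierarchical one. That limits how far the figures can be pressed. But grouping by risk level, whether by a fixed term or a random effect with three units, puts no correlation between the answers of one woman, and that is the omission at issue.

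A third argument is that a condensed article leaves random-effects detail to the full protocol. That disposes of any complaint about missing detail. It does not cover a nesting that is stated, and stated in reverse.

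Two stronger inferences also fail. One is that the risk-reduction effect is not estimated from within-woman changes. Every woman answers every scenario, so the contrast between scenarios is already a within-woman contrast; only its standard error would be off, and too large. The other is that the fixed low-medium-high order is part of this error. That order does confound risk level with presentation order, but it is the same for every woman and has no bearing on the nesting. It is a separate design point.

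**Conclusion.** The nesting as written is wrong and contradicts the description of the scenarios. That conclusion needs no assumption.

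The consequence is conditional. With a literal fit and no woman-level term, standard errors for the four woman-level determinants would be too small by roughly 1.1 to 1.5 times, with type I error of about 8% to 19%. The standard error for the risk-reduction effect would be too large. The size depends on the assumed within-woman correlation; the direction needs only that a woman's answers are positively correlated, which is very likely here.

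The importance is moderate. Willingness in the hypothetical scenarios is a secondary outcome, and the regression has no stated power or decision rule. The primary mean VTE threshold with its confidence interval, the threshold regression and the real-life logistic model each use one observation per woman and are unaffected.

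**What to change.** Replace the two sentences on levels with an explicit statement. Level 1 is the choice in each scenario, with scenario (low, medium, high) as a level-1 covariate. Level 2 is the woman, with a random intercept and with VTE experience, LMWH experience, education and site as level-2 covariates.

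GEE clustered on the woman is an acceptable alternative. Name one of the two before analysis, because the random-intercept model gives woman-specific odds ratios and GEE gives population-averaged ones.

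The cost is a change of wording and the matching analysis code. No new data, extra participants or change to the interview is needed.
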